## Abstract

**Introduction:**

In Sidama, Ethiopia, animal-source foods can be difficult to access. Milk has important nutrients for child growth, but carries the risk of aflatoxin M_1_ (AFM_1_) contamination. AFM_1_ is a metabolite of the mycotoxin aflatoxin B_1_ (AFB_1_) in dairy feed; cows secrete AFM_1_ in milk when their feed contains AFB_1_ produced by *Aspergillus* fungi in maize, nuts and oilseeds. It is unknown whether AFM_1_ compromises child growth and health.

**Methods and analysis:**

This protocol paper describes our study in Sidama to determine the impact of milk consumption and AFM_1_ on child growth in the first 18 months of life. We will collect baseline and end-line data on dairy production, socioeconomic and nutritional factors of 1000 dairy-owning households with children ages 6–18 months at baseline; and gather samples of milk and dairy feed and child anthropometrics. We will conduct phone interviews every 6 months to ascertain changes in practices or child health. Dairy feed will be tested for AFB_1_; milk for AFM_1_, pathogens and nutrients. Controlling for herd size, socioeconomic, nutritional and behavioural factors, we will determine the association between child anthropometrics and milk consumption, as well as AFM_1_ exposure. We will examine whether AFM_1_ exposure affects child growth in the first 18 months of life, and weigh the benefits and risks of milk consumption.

**Ethics and dissemination:**

The protocol is approved by the Institutional Review Boards of the Ethiopian Public Health Institute (EPHI-IRB-481–2022), Michigan State University (STUDY00007996) and International Food Policy Research Institute (DSGD-23–0102). Written informed consent will be obtained from all participants, who may withdraw from the study at any time. Confidentiality of collected data will be given high priority during each stage of data handling. The study’s findings will be disseminated through stakeholder workshops, local and international conferences, journal articles and technical reports.

Strengths and limitations of this studyThis is the first study that assesses how aflatoxin M_1_ (AFM_1_) in milk affects child growth in Ethiopia, controlling for socioeconomic, nutritional and environmental factors.This research compares the health risks of AFM_1_ with the benefits of milk consumption for children.The findings will be used to inform feasible, health risk-based policies on AFM_1_ in milk, not just in Ethiopia, but potentially in other nations worldwide.The findings of this study would not allow for causal inference or finding a toxicological mechanism because of the observational design, but would aid in the understanding of the relationship between AFM_1_ exposure and child growth.

## Introduction

Aflatoxins are secondary metabolites of the fungi *Asperfillus flavus* and *A. parasiticus*, which frequently infect food and feed crops such as maize, groundnuts, oilseeds and tree nuts.^1^ Aflatoxin B_1_ (AFB_1_) is the most toxic form of aflatoxin, and a potent liver carcinogen. Aflatoxin M_1_ (AFM_1_), a metabolite of AFB_1_, is excreted in milk when mammals consume feed contaminated with AFB_1_. Infants and young children can become exposed to AFM_1_ through dairy animal milk consumption. Although AFM_1_ is a far less potent carcinogen than AFB_1_, it may cause other health risks. Furthermore, knowledge of the tradeoff between the nutritional benefits of milk versus risks of AFM_1_ exposure in milk is currently sparse.

Globally, milk is a critically important animal source of food for infants and young children, providing a wide range of nutrients—protein, carbohydrates, fat, calcium, potassium and vitamin B_12_ among others—crucial for growth and development.^2–4^ Including milk in children’s diets is all the more important when access and affordability of other animal-sourced food such as meat and eggs are difficult.^5^ In addition, milk products are economically valuable; as the dairy value chain contributes substantially to livelihoods in semi-urban and rural areas worldwide.^6–8^

Conversely, milk can harbour multiple contaminants such as AFM_1_. AFB_1_, the parent compound of AFM_1_, may impair child growth^9^ through several pathways such as disruption of insulin-like growth factors,^10^ intestinal damage^11^ and immunosuppressive effects that increase infection susceptibility.^12 13^ Whether AFM_1_ could cause similar effects is unknown. This research study aims to fill this knowledge gap by examining the relationship between AFM_1_ exposure and growth outcomes in infants and young children in Ethiopia.

Ethiopia is an ideal setting for our proposed work, as it faces important tradeoffs between the benefits of milk production and consumption and AFM_1_ risk. Ethiopia has recently adopted a strict standard for AFM_1_ in milk, 0.5 µg/L (Ethiopian Standards Agency CES-278), which is often exceeded in raw milk samples from Ethiopia as shown by mean AFM_1_ levels ranging between 0.41 and 0.69 µg/L with a range of 0.028–4.96 µg/L.^14^ The action level for AFM_1_ in milk in the USA is the same, at 0.5 µg/L^15^; while the European Union standard is 0.05 µg/L.^16^ The recent lack of evidence linking AFM_1_ to cancer has led to the question of whether the standards set are reasonable.^12^ Moreover, dairy markets are important in Ethiopian livelihoods, particularly in rural areas where dairy is an important source of supplemental income.^17^ If excessively strict AFM_1_ standards are enforced in Ethiopian dairy markets, it could result in both economic losses from discarded milk, and nutritional losses due to negative public perception against milk consumption.^12 18^

To assess the relationship between AFM_1_ exposure and growth outcomes and the potential benefits and risks of AFM_1_ in milk in Ethiopia, we use a prospective longitudinal cohort design. Here, we describe the objectives, methods and expected outcomes of this study.

## Objectives

Our goal is to determine whether AFM_1_ exposure through milk consumption is associated with child growth impairment over a period of 18 months in early childhood; then to compare this risk with the benefits of milk consumption. This evidence will inform policy recommendations for AFM_1_ regulation in dairy products in Ethiopia. The specific objectives of this study are to:

Determine the association between milk consumption and growth outcomes in children 6–36 months of age.Examine the association between AFM_1_ exposure and growth outcomes in children 6–36 months of age who consume milk.Compare the health benefits and risks associated with dairy consumption in relation to child growth outcomes.Develop policy recommendations for regulating AFM_1_ and communicating dairy benefits and risks.

## Methods and analysis

The study will be carried out in two parts. First, we will conduct formative research with semi-structured interviews of families with young children aged 6–18 months who also own dairy cows, to assess dairy management practices (especially those related to cattle feeds) and dairy production and consumption practices in the Sidama region in Ethiopia. Second, we will use findings to inform the main quantitative arm of the study as outlined in the four objectives above.

### Formative research study

Limited prior evidence suggests that AFM_1_ contamination in milk is widespread in Ethiopia.^19 20^ There is also limited evidence on farmers’ awareness of AFB_1_ contamination in feed and consequently AFM_1_ contamination in milk, feed and storage practices used to reduce contamination (if any), and behaviours of children’s caregivers in relation to these issues. Hence, we conducted a formative research study to gauge the AFM_1_ risk in cow milk in peri-urban and rural study areas with high rates of cattle ownership and variation in market access to feed. Through the formative research, we gained an understanding of cow feeding issues such as feed type, variation and storage; as well as children’s dairy consumption patterns and complementary feeding practices. The findings of the formative research informed the sampling strategy and the questionnaire design of the main study. The results of the formative research are presented in a different research paper.^21^

### Study design and data collection

The target group of the main study is 1000 caregivers and their children aged 6–18 months from urban or peri-urban households that raise dairy cattle. In the initial visit, a baseline survey will be used to collect data such as anthropometric measurements, child’s diet and socio-demographic factors among other data. After the baseline survey, short phone-based interviews will be carried out every 6 months to assess the variability in the child’s milk consumption and dairy production factors. Our end-line visit, mainly to collect data on child’s anthropometric measurements, will be carried out 18 months after the initial visit. **Patient and public involvement**: the interview results from the formative research described above on public participants in Sidama, Ethiopia, aided the selection of households in the second part of our work.

### Study setting

The study will be conducted in two districts, Wondo Genet and Hawassa Zuria of Sidama region in Ethiopia (figure 1). These districts are purposely selected due to the common practice of using cow’s milk as complementary food for young children, availability of commercial milk, potential for AFB_1_ contamination in livestock feeds and variation in market access to feed.

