### Sampling procedures

Our formative research found that feed ingredients and type varied by herd size and season. Based on these findings, we will classify the dairy cow-owning households into small herd size (one to three cattle) and large herd size (four or more cattle) and randomly select a total of 500 households each from both groups. The two study districts have a list of herd sizes to provide the sampling frame. Within these two groups, all households have an equal chance of being selected.

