### Control variables

Data on the control variables will be collected during the survey visits and will include characteristics that are likely to be correlated with child growth outcomes and child’s milk intake. This includes variables such child’s sex, age and diet, parent’s education, household wealth index, milk’s nutrient content, pathogens in milk and child’s maize consumption.

A questionnaire will collect information about child, parent and household characteristics. Information on children’s diet comes from the 24-hour recall survey. We will control for children’s diets by calculating caloric intake variables from eight food groups: (1) Breastmilk, (2) Grains, roots and tubers, (3) Pulses, nuts and seeds, (4) Dairy products, (5) Flesh foods (meats, fish, poultry, organ meats), (6) Eggs, (7) Vitamin-A rich fruits and vegetables and (8) other fruits and vegetables.^26^ Additionally, we will collect detailed data on the non-standard recipe’s ingredients for all mixed dishes that were prepared at home and use standard recipes from the National Food and Nutrition baseline survey dietary data set to assess the amount of food consumed.^27^ The dietary surveys will be administered outside of major Ethiopian Orthodox fasting periods during which dairy household availability and consumption may decline sharply.^28^

One potential source of measurement error in linking food consumption to child growth is within-person variability in consumption. Since linear growth in young children depends on long-term dietary quantity and quality, the 24-hour recall method is imperfect for capturing variability in diets over time.^29^ To address this, we will conduct interim phone surveys every 6 months to ask caregivers about the 24-hour milk consumption and weekly recall of the child’s diet diversity, and assess basic milk production. These higher frequency measurements will be used to assess seasonality, variability, and to adjust for consumption variability in our analysis.

A subsample of 500 livestock feed samples will be collected for testing AFB_1_. Detection of AFB_1_ in feed samples will be achieved using the Helica Low Matrix Aflatoxin B_1_ competitive ELISA kit, manufactured by Helica Biosystems, Santa Ana, California, USA, listed under Catalogue Number 981BAFL01LM-96 and using procedures outlined by them.^30^

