### Data analysis

#### Empirical approach

Descriptive analysis will focus on computing frequencies and percentages for categorical variables and summary statistics (like means, medians SD, IQR) for summarising continuous variables. To determine the association between dairy consumption and growth outcomes in children 6–18 months of age at the baseline, we will specify a least squares regression model as:

(1)
$$Y_{iv}=\alpha +\beta_{M}M_{iv}+X_{iv}^{\prime }\delta +\varepsilon_{iv}$$

where 
$Y_{iv}$
 is the anthropometric outcome for a child *i* residing in enumeration area *v* measured at various time points. Variable 
$M_{iv}$
 measures the child’s milk intake at various time points. The regression controls for child, parent and household characteristics that are captured in vector 
$X_{iv}$
. These control variables are observable characteristics that are likely to be correlated both with a child’s milk intake and his/her growth outcomes. The terms 
α
 and 
$\varepsilon_{iv}$
 in equation (1) represent the intercept and error term, respectively. The coefficient 
$\beta_{M}$
 quantifies the conditional association between a child’s milk intake and subsequent growth outcome, measured either as HAZ at the end line or as change in HAZ between the baseline and end-line surveys. Considering previous evidence from Ethiopia and elsewhere, we expect 
$\beta_{M}$
 >0.

To determine the association between AFM_1_ levels in milk and nutrient density in milk, we will conduct a univariate analysis on each of the macronutrients and micronutrients and then carryout bivariate tests with AFM_1_ levels in the same samples and determine if and how they are associated with each other.

To determine the association between AFM_1_ exposure and growth outcomes in children 6–36 months of age who consume dairy, we will test whether the consumption of AFM_1_-contaminated milk is associated with lower HAZ (ie, more growth faltering) controlling for confounders and co-factors, including the amount of milk consumed and nutrient content and pathogens in the milk. We will append equation (1) with a variable capturing the child’s AFM_1_ exposure (variable 
$A_{iv}$
). In this model, we also control for the estimated macronutrient and micronutrient content and pathogens (vector 
$C_{iv}^{`}$
) in the milk sample collected at the baseline from the household in which the child resides. We will also control for the child’s maize consumption (vector 
$H_{iv}^{`}$

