), since maize is also likely to be contaminated by aflatoxins in the Ethiopian setting.^34–37^ The estimated model can be defined as:

(2)
$$Y_{iv}=\alpha +\beta_{M}M_{iv}+\beta_{A}A_{iv}+\beta_{C}C_{iv}^{\prime }+X_{iv}^{\prime }\delta +H_{iv}^{\prime }\vartheta +\varepsilon_{iv}.$$

We expect that 
$\beta_{A}$
 < 0.

To compare the health benefits versus risks of dairy consumption in child growth outcomes, we will use the regression estimates from equation (2) to conduct joint hypothesis tests for 
$\beta_{M}$
 and 
$\beta_{A}$
, where the null hypothesis is that both of these coefficients are zero, to inform benefit-risk tradeoff of dairy consumption in the context of AFM_1_.

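### The AFM1 and milk models carry an enumeration-area subscript but no location term, so any district difference in both AFM1 and HAZ that survives the listed controls goes into the coefficients

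*Protocol article*

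**What the plan says.** Under Study setting, the article states: "The study will be conducted in two districts, Wondo Genet and Hawassa Zuria of Sidama region in Ethiopia". It gives four reasons for the choice: use of cow's milk as a complementary food, availability of commercial milk, and "potential for AFB_1_ contamination in livestock feeds and variation in market access to feed". The last two concern the source of AFM1.

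Under Empirical approach, the outcome "is the anthropometric outcome for a child *i* residing in enumeration area *v* measured at various time points". The area label is thus carried in the notation. On adjustment the text says: "The regression controls for child, parent and household characteristics that are captured in vector" X. Equation (1) contains an intercept, milk intake, X and an error term. Equation (2) adds AFM1 exposure, milk nutrients and pathogens, and maize consumption. Both have a single intercept, and neither has a term for district or area.

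The Control variables section names no location variable: "This includes variables such child’s sex, age and diet, parent’s education, household wealth index, milk’s nutrient content, pathogens in milk and child’s maize consumption". Nor does the abstract: "Controlling for herd size, socioeconomic, nutritional and behavioural factors". The strengths list claims control for environmental factors, but apart from milk pathogens and maize intake no such variable is named.

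The growth outcome is taken either as HAZ at end line or as change in HAZ from baseline to end line.

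**The concern.** District is known for every child, and it may be related to both exposure and outcome. Places that differ in feed markets may also differ in food markets, services and disease environment, which a household wealth index and parental education capture only in part. With one intercept, the fitted AFM1 slope mixes two comparisons: children within the same district, and one district against the other. The second rests on two sites and cannot separate AFM1 from anything else that distinguishes them.

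The Discussion says the design aims to limit bias by controlling for observable confounders, and that the results will inform AFM1 standards. A between-district gap read as an AFM1 effect, or one that hides such an effect, would reach that policy use. No stated analysis shows whether the association holds within a district.

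**Working it through.** The plan gives no figure on this point to reproduce. The check asks how large the district gaps must be to matter.

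**Inputs from the article (Sample size calculations).** HAZ SD 1.56; about 1000 children; 10% attrition, so 1000 × 0.9 = 900 analysed; 5% significance level, taken as two-sided because sidedness is not stated.

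**Assumptions.** Two districts of equal size; no true AFM1 effect; AFM1 scaled to a total SD of 1. The districts differ by g SD in AFM1 and by h in HAZ. Both gaps are what remains after the listed controls.

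**Formulas.**
- Spurious slope when district is omitted: g × h / 4, in HAZ per SD of AFM1.
- Standard error: 1.56 / √900 = 0.052.
- Rejection rate: P(|Z + slope/SE| > 1.96).

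Example: g = 0.5 and h = 0.3 give 0.5 × 0.3 / 4 = 0.0375. Then 0.0375 / 0.052 = 0.72, and the rejection rate is 11.1%.

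| g (SD AFM1) | h (HAZ) | Spurious slope | Slope/SE, n = 900 | Rejection, n = 900 | Rejection, n = 600 |
|---|---|---|---|---|---|
| 0.3 | 0.2 | 0.015 | 0.29 | 6.0% | 5.6% |
| 0.5 | 0.2 | 0.025 | 0.48 | 7.7% | 6.8% |
| 0.5 | 0.3 | 0.0375 | 0.72 | 11.1% | 9.1% |
| 0.8 | 0.3 | 0.060 | 1.15 | 21.1% | 15.6% |
| 0.8 | 0.5 | 0.100 | 1.92 | 48.5% | 34.9% |

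The n = 600 column stands for an analysis restricted to milk consumers. The article does not give their share, so 600 is only an illustration.

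**Simulation check (4000 runs, n = 900).** Without a district term, rejection was 6.0%, 11.1%, 21.5% and 46.5% for (g, h) = (0.3, 0.2), (0.5, 0.3), (0.8, 0.3) and (0.8, 0.5). With a district term it was 5.2% to 5.5% in all four.

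**Masking direction.** At n = 900 the slope detectable with 80% power is (1.96 + 0.84) × 0.052 ≈ 0.146 HAZ per SD of AFM1. Suppose the true slope is −0.146 and the bias is upward. A bias of 0.025 leaves 0.121 / 0.052 = 2.32 standard errors, and power is Φ(2.32 − 1.96) ≈ 64%. A bias of 0.0375 leaves 2.08 standard errors, and power is about 55%.

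**Cost of the district term.** The variance inflation factor is 1 / (1 − (g/2)²): 1.02 at g = 0.3, 1.07 at 0.5 and 1.19 at 0.8. The standard error rises by the square root, about 1%, 3% and 9%.

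**The case against.** The list of controls is worded as examples and is visibly incomplete: the abstract promises adjustment for herd size, which the list omits. This is a condensed article, and an analysis plan that is not shown could include a district term. That stands as a reason not to say the authors will ignore location. It does not remove the point, because the models are written out term by term, X is defined by type of characteristic, and the area subscript is carried without being used.

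A reader might infer that the districts were chosen because feed access, and hence AFM1, differs between them. The article does not support this. Feed market access is one of four reasons, and the text does not say whether it varies between or within the districts. The drivers of feed variation named under Sampling procedures are herd size and season.

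The change-in-HAZ outcome is a real protection. It removes any district gap in HAZ level that is constant over time. It does not remove a difference in growth rate, and the alternative outcome, end-line HAZ, lacks the protection altogether.

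The gaps in the table are assumptions. They must be residual after wealth, education, diet, maize and milk composition, so large values need more justification than small ones. The AFM1 model covers only milk consumers, which lowers the rates shown.

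A reader might also infer that measurers or ELISA plates line up with district, or that the sample should be fixed by district. The article does not say how staff or plates are assigned, and the assays are run in duplicate at one laboratory. Sampling is by herd size ("randomly select a total of 500 households each from both groups"), with equal chances within each group. A district mix that differs between herd groups is not in itself a flaw. These readings are not part of this point.

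**Conclusion.** The specification as printed has no location term in a two-district study where part of the reason for choosing the sites bears on the exposure. The resulting bias is possible, not demonstrated: it requires AFM1 and HAZ (or growth rate, for the change outcome) both to differ by district after adjustment. It can run either way, and the masking direction works against the article's expectation of a negative AFM1 coefficient.

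For moderate residual gaps (0.5 SD in AFM1, 0.2 to 0.3 in HAZ) the effect is modest: a spurious slope of 0.025 to 0.0375 HAZ per SD of AFM1, and rejection of about 8% to 11% instead of 5% with 900 children. Gaps of 0.3 SD and 0.2 HAZ barely matter (6%). Gaps of 0.8 SD and 0.5 HAZ would matter a great deal (about 47% to 49%), but nothing in the article indicates gaps of that size. The point is worth acting on because the remedy is nearly free, not because serious bias has been shown.

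**What to change.** Add a district indicator to equations (1) and (2) and name this as the main specification, for both end-line HAZ and change in HAZ. State enumeration-area fixed effects as a robustness check. Report the AFM1 coefficient within each district as descriptive only: with about 450 children each, the standard error is 1.56 / √450 = 0.074, and the slope detectable with 80% power is about 0.21 HAZ per SD of AFM1.

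The cost is one model term using information already indexed, with no extra children, visits or tests. The variance inflation is about 1.02 to 1.19 for AFM1 gaps of 0.3 to 0.8 SD. Enumeration-area effects cost more, because they discard all between-area variation in AFM1. The article does not give the number of areas, so that cost cannot be calculated here, and it is why they serve as the check and not as the main model.
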